##### 11. Privacy / Confidentiality Protections.

Interview and focus group data will be transcribed and imported into qualitative data analysis software for analysis (e.g. nVivo, Dedoose). All identifying information will be removed from transcriptions. Study IDs will be substituted for names. All participant and quantifiable study data will be stored in a HIPAA compliant manner, such as a password-protected electronic database (REDCap) and/or in a file on a secure Rutgers server accessible only by the PI and key study personnel. Collected data will only be identified via a study ID that will serve as a link to identifiable information in a separate file on a password-protected, secure, Rutgers server or in a separate part of the password-protected electronic database (REDCap). Data will be analyzed in aggregate only and no identities will be revealed. For qualitative reporting, participants may be identified by pseudonyms or general descriptors (e.g. “daughter care partner,” “physician”).

##### 12. Data Use Agreement.

A subaward agreement outlines the scope of work and research data to be shared between VNS Health and Rutgers (see “Subaward Agreement.”)

##### 13. Rutgers IRB Approval.

Rutgers IRB approval is pending and will be submitted to the VNS Health IRB prior to data collection or sharing begins.

##### 14. Reporting.

The PI, [name], will adhere to VNS Health IRB reporting requirements, including submitting a study closure report within 60 days of the end of primary data collection. The PI will also submit a summary of main project findings when available.

##### APPENDIX: Data Collection Tools

# Aims 1-3. Demographic Questions (Baseline)

1. What is your date of birth?
2. What is your gender?

□ Male

□ Female

□ Other

1. What is your race/ethnicity?

□ White

□ Black or African American

□ Asian

□ American Indian or Alaska Native

□ Native Hawaiian or other Pacific Islander

□ Multi-racial (specify)

□ Other, please specify

□ Don’t know/unsure

□ Prefer not to answer

1. Are you of Hispanic, Latino/a, or Spanish origin?

□ Yes

□ No

□ Prefer not to answer

□ Don’t know/unsure

1. (If YES to Q4). What is your family’s country of origin? [if multiple indicated, ask person to select the one with which he/she most strongly identifies]

□ US

□ Puerto Rico

□ Mexico

□ Dominican Republic

□ Cuba

□ Other (specify):

□ Don’t know/unsure

1. What is your religion?

□ Catholic

□ Baptist

□ Protestant

□ Jewish

□ Muslim

□ Pentecostal

□ Atheist

□ Agnostic

□ Other (specify)

□ Prefer not to answer

□ Don’t know/unsure

Other:________________________________

1. What was the highest education level you completed?

□ Some elementary school

□ Completed elementary school

□ Some high school

□ High school or GED

□ Some college

□ College degree

□ Post-graduate but no degree

□ Graduate degree

□ Prefer not to answer

□ Don’t know/unsure

1. Are you currently employed?

□ Yes

□ No

□ Prefer not to answer

□ Don’t know/unsure

(If no, skip to question 9)

1. If you are employed, is it:

□ Part-time

□ Full-time

1. Are you retired?

□ Yes

□ No

□ Prefer not to answer

□ Don’t know/unsure

1. What is/was your occupation?

11a. How long have you been in this occupation? _______________

1. We ask about participants’ socioeconomic backgrounds because we think it is important to understand how people from different backgrounds differ in their experiences with dementia and hospice. Would you mind telling me the annual, combined income range for all family members in your household?

What is your annual income, before taxes?

□ Less than $25,000

□ $25,000 to $49,999

□ $50,000 to $74,999

□ $75,000 to $149,999

□ $150,000 or more

□ Prefer not to answer

□ Don’t know/unsure

1. What is your marital status?

□ Single

□ Married

□ A member of an unmarried couple

□ Divorced

□ Separated

□ Never married

□ Widowed

□ Prefer not to answer

□ Don’t know/unsure

1. Do you have children?

□ Yes

□ No

□ Prefer not to answer

□ Don’t know/unsure

15. (If YES to Q14). How many children?

1. What is your role?

- Family Caregiver
- Clinician
- Other (specify)

## ***Additional question for clinicians***

1. What is your occupation? (collected as part of initial screening)
   - - 1. Nurse practitioner
       2. Nurse
       3. social worker
       4. other (please specify)
2. How long have you been working in hospice care?
3. How often do you typically see a patient during their hospice stay?
4. One time
5. A few times, as needed
6. Monthly
7. Every two weeks
8. Weekly, or more often

***Additional questions for FCP:***

Now I would like to ask you some questions about your experience providing help and support to your loved one.

1. What is your relationship to your family member? I am his/her:

□ Spouse / Partner

□ Daughter

□ Son

□ Daughter-in-law

□ Son-in-law

□ Sister

□ Brother

□ Sister-in-law

□ Brother-in-law

□ Granddaughter

□ Grandson

□ Other(specify)

1. For how long have you been providing help or care to your family member?
2. On average, how many hours a week do you help your family member?

□ < 8 hours

□ 8 to <15 hours

□ 15 to <30 hours

□ 30 hours or more

□ 24 hours a day, 7 days a week

1. In the past two weeks, how often have you helped your family member with self-care tasks, including dressing, bathing, toileting, eating, or getting out of bed/around the home?

□ Daily/Almost every day

□ 2-3 times a week

□ 2-3 times in the last two weeks

□ I have not helped with any of these

1. In the past two weeks, how often have you helped your family member with activities including cooking, cleaning, providing transportation, laundry, or managing finances?

□ Daily/Almost every day

□ 2-3 times a week

□ 2-3 times in the last two weeks

□ I have not helped with any of these

1. In the past two weeks, how often have you helped your family member manage their health including managing or giving medications or coordinating with healthcare providers such as hospice or doctor’s offices?

□ Daily/Almost every day

□ 2-3 times a week

□ 2-3 times in the last two weeks

□ I have not helped with any of these

# Aim 1. Think Aloud Interview (Round 1 feedback)

Thank you again for your time and help with this project. The goal of the project is to improve educational videos and an assessment tool to improve home hospice care and support for persons with dementia and their families. The videos are designed to provide information to hospice nurses and social workers. The assessment tool is designed to be completed in conversation with hospice nurses or social workers and families of persons with dementia. We would like to get your feedback on the videos and assessment tool and will use your feedback to improve them. I will ask you questions about each as we review them. Do you have any questions before we begin?

Videos

[Ask questions for each video]

1. I want to understand what you think about the video. Watch it and think about the information it contains. Tell me things you might be thinking as you watch.

What part of the video was most helpful?

Why do you think this is the most helpful?

1. Describe the message of the video in your own words.

Was there any part of the message that was confusing to you?

Are there parts of the message that you think would be helpful to a family member of a person with dementia?

1. Do you have any additional thoughts or suggestions for improving this video? This might include additional information we should include, topics you would like to see addressed or removed?
2. What do you think is the most important thing for hospice nurses and social workers to understand about the topic addressed in the video?

Do you think that was covered in the video? What additional information should we include?

The next set of questions ask about particular parts of the video.

1. Did you have difficulty understanding the narrator?

Do you have suggestions for making it easier to understand the narrator?

1. Did you have difficulty understanding the slides?

Do you have suggestions for making it easier to understand the slides?

1. Is the amount if information in the video appropriate? For example, is there too much or too little information in the video?
2. How often do you think you would watch these videos? For example, once? A few times? A different timeline?

Assessment Tool

1. What part of the assessment was most helpful?

Why do you think this is the most helpful?

1. Describe the purpose of the assessment tool in your own words.

Was there any part of the assessment tool that was confusing to you?

Are there parts of the assessment tool that you think would be helpful to a family member of a person with dementia?

1. Do you have any additional thoughts or suggestions for improving this assessment tool? This might include additional information we should include, topics you would like to see addressed or removed?

The next set of questions ask about particular parts of the assessment tool.

1. Did you have difficulty understanding the assessment tool?

Do you have suggestions for making it easier to understand the assessment tool?

1. Did you have difficulty understanding the slides?

Do you have suggestions for making it easier to understand the slides?

1. Is the amount if information in the assessment tool appropriate? For example, is there too much or too little information in the assessment tool?
2. How often do you think you would use the assessment tool? For example, once? A few times? Every time a hospice nurse or social worker visits? A different timeline?
3. What do you think is the most important thing for hospice nurses and social workers to ask about in the assessment tool?

Do you think that was covered in the video? What additional information should we include?

1. Would you be willing to use the assessment tool during a phone call or telehealth visit?

What are the benefits of using the assessment tool over the phone? During a telehealth visit?

What are the drawbacks of using the assessment tool over the phone? During a telehealth visit?

Do you have suggestions for a better method for using the assessment tool?

1. How much time should it take to complete the assessment tool?

**Aim 1. Think Aloud Questionnaire for Round 2 of Data Collection**

[Ask questions for each video]

1. We have some questions about the language used in the [video/tool].
   1. Were there words that you found confusing or that you didn’t understand?
   2. Were there words you found off-putting, or that you would not use to describe your experience?
   3. What words would you suggest in place of the ones we used?

[Prompt for reaction to the following words: progression, addiction, caregiving, burden, strain, stressor, strategy, advantage, disadvantage, etc.]

1. Are there changes you would suggest to make the [video/tool] more visually pleasing?

[Prompt for reaction to: slide color, font type, font size, visual aids (icons, photos, graphics)]

1. Are there changes you would suggest to make the [video/tool] more reflective of the hospice experience?
2. Are there changes you would suggest to make the information provided in the [video/tool] better organized or easier to follow?
3. [For relevant video] What did you think about the closed captioning? [Prompt: Did you find it helpful or distracting? Is this something you would like to see for all of the videos?]
4. Do you have other suggestions to improve the [video/tool]?
5. Is there anything you would suggest we definitely keep or do not change in the [video/tool]?

Additional questions for Assessment Tool:

1. How helpful was the video in explaining how to use the tool?
2. Do you think it is necessary to watch the video in order to use the tool correctly? Why or why not?
3. How confident would you be using the tool without having seen the video? Why do you think that?

## **Aims 2 and 3. Pre/Post Video Questions.**

Clinicians are asked these questions as part of baseline data collection upon enrollment. Relevant questions are also asked after viewing each video.

Instructions. Except where indicated, all questions are asked at study enrollment as part of baseline data collection and again after each video or upon completion of all training modules.

All questions regarding confidence are answered on a 1 (not at all confident) to 10 (extremely confident) point scale.

Confidence Questions are asked all at once pre-video and immediately following each relevant video.

(responses: 1= not confident at all, 2, 3, 4, 5=somewhat confident, 6, 7, 8, 9, 10=very confident).

1. How confident are you in providing dementia-related care to hospice patients?
2. How confident are you in providing support to family members of hospice patients living with dementia?

Nutrition video:

In thinking about your home hospice patients living with dementia and their family members:

1. How confident do you feel **assessing** a patient’s eating, drinking, and nutrition needs?
2. How confident do you feel **assessing family member education needs** with respect to eating and drinking?
3. How confident do you feel **talking with families** about a patient’s eating, drinking and nutrition when problems arise?
4. How confident do you feel **providing family members with information or education** about eating and drinking?
5. How confident do you feel **providing family members with concrete strategies or steps** they can implement to address their loved one’s eating and drinking?
6. How confident do you feel **talking with families about feeding tubes**?
7. How confident do you feel **providing families with education or information** about feeding tubes?

Pain video

In thinking about your home hospice patients living with dementia and their family members:

Pain Assessment

1. How confident do you feel **assessing** a patient’s pain?
2. How confident do you feel **assessing family member education** **needs** with respect to pain assessment?
3. How confident to you feel **talking with families** about assessing a patient’s pain or discomfort?
4. How confident do you feel **providing family members with information or education** about pain assessment?
5. How confident do you feel **providing family members with concrete strategies or steps** they can implement to assess their loved one’s pain?

Pain Management

1. How confident do you feel **managing** a patient’s pain?
2. How confident do you feel **assessing family member education needs** with respect to pain management?
3. How confident to you feel **talking with families** about managing a patient’s pain or discomfort in general?
4. How confident to you feel **talking with families** when medication problems arise?
5. How confident do you feel **talking with families** about using opioids such as morphine?
6. How confident do you feel **providing family members with information or education** about non-medication pain management?
7. How confident do you feel **providing family members with information or education** about medication to manage a patient’s pain?
8. How confident do you feel **providing family members with information or education** about morphine?
9. How confident do you feel **providing family members with concrete strategies or steps** that do not involve medication and they can implement to manage their loved one’s pain?
10. How confident do you feel **providing family members with concrete strategies or steps** involving medication and they can implement to manage their loved one’s pain?

Tool Video

In thinking about your home hospice patients living with dementia and their family members:

1. How confident do you feel **identifying family caregiver burden, stressors or worries** during routine home visits?
2. How confident do you feel **helping family caregivers** to address their burden or worries?
3. How confident do you feel **encouraging family caregivers to identify strategies** they can use to address their burden or worries?
4. How confident do you feel **identifying the pros and cons** of each strategy?
5. How confident do you feel **following up with family caregivers** about burden or worries?

(Post Tool video only)

1. After watching this video, how **confident** do you feel using the [assessment tool/worksheet] to assess family caregiver burden at initial and follow up visits?
2. How often do you plan to use the [tool/worksheet] to assess family caregiver burden?
   - - 1. Every visit
       2. Most visits
       3. Initial visit only
       4. Rarely
       5. Never (please explain)

Confidence Questions are asked all at once pre-video and immediately following each relevant video.

(responses: 1= not confident at all, 2, 3, 4, 5=somewhat confident, 6, 7, 8, 9, 10=very confident and 11 I do not conduct the hospice admission visit).

EHR Video

1. How confident do you feel recording family caregiver burden in the electronic hospice record at **admission visit**? [include option: I do not conduct the hospice admission visit].
2. How confident do you feel recording family caregiver burden in the electronic hospice record at **routine follow-up visits**?

(Pre video only)

1. How often do you record family caregiver burden at the admission visit?
2. Every visit
3. Most visits
4. Rarely
5. Never (please explain)
6. I do not conduct the hospice admission visit
7. How often do you record family caregiver burden during routine follow-up visits?
   1. Every visit
   2. Most visits
   3. Rarely
   4. Never (please explain)

(Post EHR video only)

1. How often do you plan to record family burden in the electronic hospice record?
   1. Every visit
   2. Most visits
   3. Initial visit only
   4. Rarely
   5. Never (please explain)

# Aim 2 and 3 Feasibility and Acceptability: User-Centered Design

**Family Care partners and Clinicians**

***Review of Individual Videos (Clinicians Only-to be administered post video training)***

Instructions: Now we are going to ask you some questions about each video. Thinking about the video on (*state topic*) (repeat for each video)

1. Did you have any issues accessing or viewing the video on [topic]?
   1. No
   2. Yes (please explain)
2. How much of this video did you watch?
   1. 25%
   2. 50%
   3. 75%
   4. All of it
   5. None of it
3. If 2b or 2c: I did not complete the videos because (check all that apply).

□ I had trouble understanding the videos

□ The videos were too long

□ I did not think the content of the videos was relevant to my work

□ I did not learn anything from the videos

□ I did not have time to watch the videos

□ Other (specify):

1. How helpful was the video on [topic] to you?
   1. Not at all helpful
   2. Slightly helpful
   3. Moderately helpful
   4. Helpful
   5. Very Helpful
2. Please indicate what you found helpful about the video:
3. How could we improve the video?
4. How difficult was it for you to understand the content of the video on [insert /topic] (e.g. language, ideas)?
   1. Very difficult
   2. Difficult
   3. Moderately difficult
   4. Slightly difficult
   5. Not at all difficult
5. [If participant scores >1 on the previous item]: I am going to list a few things that may have made the video difficult to understand. Indicate whether each option made the video difficult for you. Was the video difficult because the:
   1. Wording was too complicated: Y/N
   2. Ideas were too complicated: Y/N
   3. There was too much information: Y/N
   4. There was not enough information: Y/N
   5. Other (please specify): __________________________: Y/N
6. If you found the content too easy or too simple, what made it too easy?
7. What information was provided that will help you [support family members with respect to [patients' eating and drinking/pain/]/record family members’ burden in the electronic health record/assess family members' burden, stressors or worries]?
8. What additional information could be provided to help you better [support family members with respect to [patient’s' eating and drinking/pain/]/record family members’ burden in the electronic health record/support family members to reduce their burden, stressors or worries]?
9. What questions do you still have that would help you [support family members with respect to [patients' eating and drinking/pain/]/record family members’ burden in the electronic health record/support family members to reduce their burden, stressors or worries]?
10. How likely are you to use the information from the video on [topic] in your clinical practice?
    1. Very Unlikely
    2. Unlikely
    3. Neutral
    4. Likely
    5. Very likely

13a. Why or why not?

1. Overall, how satisfied are you with the video on [topic]?
   1. Very dissatisfied
   2. Dissatisfied
   3. Neutral
   4. Satisfied
   5. Very Satisfied

Instructions: Thinking about all of the videos, please answer the following questions.

*[questions 15-18 for aim 3 only]*

1. How did you watch the videos? Check all that apply.
   1. Phone
   2. Computer
   3. Tablet
   4. Other (please specify)
2. What is your preferred method of watching the videos?
   1. Phone
   2. Computer
   3. Tablet
   4. Other (please specify)
3. How difficult was it to view the videos using your preferred method?
   1. Very difficult
   2. Difficult
   3. Moderately difficult
   4. Slightly difficult
   5. Not at all difficult
4. Where were you when you were watching the videos? Check all that apply.
   1. At home
   2. Place of work
   3. During commute
   4. Car
   5. Other (please specify)
5. Who do you think it the appropriate audience for these videos? (check all that apply)
   1. Family members
   2. Hospice nurses
   3. Hospice social workers
   4. Other (please specify)
6. [If 15a]: When to you think the videos on eating and drinking and pain assessment are appropriate to share with family members?
7. Hospice admission visit
8. As issues related to eating and drinking and/or pain assessment arise
9. Other (please specify)
10. [If 15b or 15c] When do you think these videos are appropriate for hospice nurses and social workers to view? (check all that apply)
11. Onboarding for new hires
12. Annually
13. Twice a year
14. >2 times a year (specify how often)
15. These videos are not appropriate for hospice nurses and social workers
16. Thinking about the videos: there are 4 educational videos. Do you think that is:
    1. Too many videos
    2. An acceptable number of videos
    3. Not enough videos
17. If you could choose, what would be your preferred way to view the videos?
    1. On your own
    2. In a small group setting
    3. As part of clinical team meetings
    4. Other (please explain)
18. Which methods for viewing the videos would you be willing to do? (select all that apply)
    1. On your own
    2. In a small group setting
    3. As part of clinical team meetings
    4. Other (please explain)

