***Review of [Assessment Tool/Worksheet] (Clinicians and FCP)***

Instructions: Please answer the following questions about the [assessment tool/worksheet] and ways we can make it better.

1. Did you have any issues accessing or viewing the [tool/worksheet]?
   1. No
   2. Yes (please explain)
2. How helpful was the [assessment tool/worksheet]?
   1. Not at all helpful
   2. Slightly helpful
   3. Moderately helpful
   4. Helpful
   5. Very Helpful
3. Please indicate what you found helpful about the [tool/worksheet].
4. How can we improve the [tool/worksheet]?
5. How difficult was it for you to understand the content of the [assessment tool/worksheet] (e.g. language, ideas)?
   1. Very difficult
   2. Difficult
   3. Moderately difficult
   4. Slightly difficult
   5. Not at all difficult
6. I am going to list a few things that may have made the video difficult to understand. Indicate whether each option made the video difficult for you. Was the video difficult because the:
   1. Wording was too complicated: Y/N
   2. Ideas were too complicated: Y/N
   3. There was too much information: Y/N
   4. There was not enough information: Y/N
   5. Other: __________________________: Y/N
7. If you found the content too easy or too simple, what made it too easy?
8. How helpful was the video in explaining how to use the [tool/worksheet]?
   1. Very helpful
   2. Somewhat helpful
   3. Neither helpful nor unhelpful
   4. Somewhat unhelpful
   5. Not at all helpful
9. Do you think it is necessary to watch the video in order to use the [tool/worksheet] correctly? Why or why not?
10. How confident would you be using the [tool/worksheet] without having seen the video?

a. Not confident at all

b. Not very confident

c. Somewhat confident

d. Confident

e. Very confident

Why do you think that?

1. [clinicians only] How likely are you to use the information [assessment tool/worksheet] in your clinical practice?
   1. Very Unlikely
   2. Unlikely
   3. Neutral
   4. Likely
   5. Very likely

11a. Why or why not?

1. Overall, how satisfied are you with the [assessment tool/worksheet]?
   1. Very dissatisfied
   2. Dissatisfied
   3. Neutral
   4. Satisfied
   5. Very Satisfied

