   2. No
8. [Intervention arm only if 6 b] Why didn’t you record family member burden in the electronic hospice record?
   1. I did not know I was supposed to do this.
   2. I do now know how to do this.
   3. I forgot.
   4. I did not have time.
   5. This wasn’t an appropriate visit for me to ask questions related to burden
   6. Other (please explain)
9. [Intervention arm only if 6 a]. Did you have any issues recording family member burden in the electronic hospice record?
   1. No
   2. Yes (please explain)
10. Additional comments or explanation.

| ***Table 2. Additional Feasibility and Fidelity Measures*** |  |
| --- | --- |
| **Feasibility and Fidelity Items** | **Measurements** |
| 1. Accrual rates | Number of potential participants contacted,  Percent of contacted enrolled  Number enrolled |
| 2. Attrition rates | Number enrolled,  Number and percent dropped out |
| 3. Adherence to the study protocol | Number and percent of clinicians:  1. viewing3 or more of the videos,  2. viewing more than 80% of each video,  3. using the tool more than 75% of the time,  4. number and percent of family care partners using the tool,  5. number of times family care partners are using the tool |
| 4. Number of educational video views | Total number of views,  Total number of unique viewers |
| 5. Frequency of issues related to viewing videos | Number of times clinicians report issues watching the video |
| 6. Types of issues related to viewing videos | Issues described by clinicians |
| 7. Number of assessment tool initial uses | Number of care partners with whom clinicians use the tool |
| 8. Number of assessment tool follow-up uses | Number of times clinicians use the tool as a follow-up |
| 9. Frequency of issues using assessment tool | Number of times clinicians report issues using the tool,  Number of times family care partners report issues using the tool |
| 10. Types of issues using assessment tool | Types of issues described by clinicians,  Types of issues described by family care partners |
| 11. Number of EHR burden reports | Number of times family care partner burden is recorded in the EHR from enrolled care partners |
| 12. Frequency of issues using EHR burden reports | Number of times clinicians report burden in the EHR |
| 13. Types of issues using EHR burden reports | Types of issues clinicians report recording burden in the EHR |

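### Three feasibility items in the appendix branch on the wrong answer or count the wrong thing, so explanatory data on video non-completion and EHR burden recording would be lost or mislabelled

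*Protocol*

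**What the plan says.** The forms are printed in the Protocol appendix with their skip rules, and Table 2 there defines the feasibility and fidelity measures.

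- **Review of Individual Videos.** Item 2 asks "How much of this video did you watch" and offers 25%, 50%, 75%, all or none. Item 3, the checklist of reasons for stopping, opens "If 2b or 2c: I did not complete the videos because".
- **Clinician Post-Visit Fidelity Assessment Form.** Item 6 is free text on the challenge the family member named. Item 7 is the Yes/No on whether burden was recorded in the hospice record. Item 8 (why it was not recorded) carries the condition "Intervention arm only if 6 b". Item 9 (issues in recording it) carries the matching condition on 6 a.
- **Table 2, row 12.** The label is frequency of issues using EHR burden reports. The measurement is "Number of times clinicians report burden in the EHR".

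Three smaller items belong to the same set.

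- **Video difficulty.** The answers are printed from very difficult (first) to not at all difficult (fifth), and the follow-up applies "If participant scores >1 on the previous item".
- **Audience follow-ups.** These depend on 15a, and on 15b or 15c.
- **Tool review.** It is headed for clinicians and care partners alike, yet it says "I am going to list a few things that may have made the video difficult to understand".

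**The concern.** Feasibility and acceptability are a stated aim of the pilot RCT (Section 2, Aim 3), and Section 9 says they will be assessed from viewing, training completion, tool use and the feasibility questionnaire. The follow-up questions explain a shortfall: why a clinician stopped watching, or why burden was not entered. If their conditions are programmed as printed, some of those clinicians are never asked. A Table 2 row that counts entries under a label of issues would report uptake as if it were trouble. These are errors in the printed instruments themselves, not detail that the protocol could leave to an analysis plan.

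**Working it through.** There is no sample size or test statistic to reproduce. The check is to lay each condition beside the answers it is meant to select and count the matches. Option letters are taken by position.

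| Item | Answers that should trigger it | Answers the printed rule selects | After correction |
|---|---|---|---|
| Reasons for not finishing a video | 2a (25%), 2b (50%), 2c (75%), 2e (none): 4 | 2b, 2c: 2 of 4 | 4 of 4 |
| Why burden was not recorded (item 8) | 7b: 1 | 6 b does not exist: 0 of 1 | 1 of 1 |
| Issues recording burden (item 9) | 7a: 1 | 6 a does not exist: 0 of 1 | 1 of 1 |

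**Video non-completion.** Five answers are offered and one is complete viewing, leaving four. A rule naming two letters cannot cover four answers, however they are lettered. All four also fall short of the Table 2 adherence criterion of viewing more than 80% of each video, so the clinicians left out (25% and none) are among those who fail it.

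For scale, Section 2 plans about 12 and at most 18 intervention clinicians.
- With 12, 8/12 = 66.7% misses the >70% completion target and 9/12 = 75% meets it, so a miss means at least 12 − 8 = 4 non-completers.
- With 18, 12/18 = 66.7% misses and 13/18 = 72.2% meets it, so a miss means at least 18 − 12 = 6.

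The explanation of a missed target may thus rest on a handful of people. How many would answer 25% or none is not given in the document and is not estimated here.

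**EHR follow-ups.** The post-visit form is numbered continuously from 1 to 10. Its other conditions (3 d-f and 3 a-c) point to the right item. Only the two EHR conditions are one item out, which suggests a reference not updated when an item was inserted.

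**Table 2 row 12.** Compare its neighbours. Row 5 (issues viewing videos) and row 9 (issues using the tool) count the times that issues are reported. Row 11 counts the times burden is recorded in the EHR. Row 12 has the label of the first kind and the measurement of the second, so no row counts EHR-recording issues.

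**Difficulty follow-up.** If scores follow printed order, a score above 1 selects answers 2 to 5: it misses very difficult and includes not at all difficult, catching 3 of the 4 answers that report difficulty. If the item is reverse coded, the same rule selects exactly the 4 that report difficulty. The form does not say which applies.

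**Audience follow-ups.** The form contains a 13a and marks items 15 to 18 as Aim 3 only. Counting from there, item 15 is the viewing device and the audience question is item 19. In the Aim 2 version, with those four items absent, the audience question becomes item 15.

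**The case against.** The strongest reply is that this is proofreading of skip patterns, and that several tempting inferences go too far. Much of that stands.

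- **Difficulty.** A reader might infer that clinicians who found a video very difficult are certainly dropped. The document does not support that. The same five-point scale carries a reverse-code note in the post-intervention clinician form, and under that coding the rule is right. The note is missing from the video item, so the defensible point is that the coding must be stated.
- **Tool non-use.** A reader might infer that reasons for not using the tool are lost. They are not: item 4 of the post-visit form asks for them after 3 d-f, which includes the answer that the tool was not used.
- **Direction.** A reader might infer that barriers will look milder. Omitted reasons could have that effect, but row 12 errs the other way by labelling entries as issues, and the remaining items have no direction.
- **Total loss.** A reader might infer that nothing would be learned about EHR problems. Item 10 of the post-visit form takes open comments. For videos, access problems are asked of everyone with room to explain.
- **Audience items.** The 15a reference is out of date only for Aim 3, and it concerns when to show the videos, not barriers.
- **Later revision.** The Aim 2 section says data collection will be modified before the RCT. That may have happened in the database, but the printed forms are labelled for Aims 2 and 3 and still carry these rules.

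Row 12 may simply have lost a word. That explains the error but does not remove it, since the table is the definition of the measure. The non-completion rule, the EHR conditions and row 12 are wrong under any reading.

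**Conclusion.** Three items are wrong as written and should be corrected. The non-completion rule reaches 2 of 4 incomplete-viewing answers, the two EHR conditions match no answer, and row 12 nearly duplicates row 11 in place of counting issues. The consequence is limited to explanatory feasibility data on video non-completion and EHR recording, and it arises only if the forms are programmed and the table applied as printed. The >70% hypotheses rest on completion, use, usefulness and satisfaction items that these conditions do not alter. The Zarit burden analysis does not draw on them. No overall direction of bias is claimed. The difficulty, audience and tool-review wording are lesser corrections.

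**What to change.** Main corrections:

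1. Ask the non-completion reasons after 2a, 2b, 2c or 2e.
2. Condition post-visit item 8 on 7b and item 9 on 7a.
3. Redefine Table 2 row 12 as the number of times clinicians report an issue recording burden in the EHR, taken from post-visit item 9. This depends on step 2, because item 9 yields nothing while its condition points to item 6.

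Lesser corrections:

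4. State the coding of the video-difficulty item and word its follow-up to fire for every answer except not at all difficult. Naming the answer avoids a new numeric cut-off that would be wrong under the other coding.
5. In the Aim 3 version, point the audience follow-ups to item 19.
6. In the tool review, replace video with tool/worksheet in the difficulty list, and limit the questions about the video to clinicians.

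The cost is a few branching edits in the survey database, some wording changes and one table row, as a minor amendment. Section 6 mentions clinicians already enrolled in May 2024, so first check how the live forms are programmed. If they follow the printed rules, record the date of correction, so that unasked items before it are reported as not collected and not as absence of problems.
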